**4.5 Planned duration of individual participation and description of the trial calendar:**

**Duration of individual study participation** = 9 months (duration of prenatal care, delivery, and the neonatal period (by definition, up to 28 days of life if necessary)

**Planned study duration** = 36 months.

**Duration of inclusion**: 27 months

**Trial calendar:**

| Mother | | | | | |  | Newborn | |
| --- | --- | --- | --- | --- | --- | --- | --- | --- |
|  | Pregnancy  Weight, BP, proteinuria: monthly | | | | | Delivery | Postpartum period | |
|  | | | | |  | 3-7 days | |
| Date | 1st visit | 2nd visit | 24-28 weeks | 32 weeks | 37 weeks |  | D0 | D2-3 |
| Procedures | BMI  BP reading  information  orientation | Consent to inclusion  Weight  BP reading | Weight  BP reading | Ultrasound: EFW |  | Weight, height, head circumference  Apgar  Cord blood* | Examination  clinical | Clinical examination  Skinfolds*  Weight, height, head circumference  Feeding |
| Samples |  | Blood glucose  fasting (for the obese women) | Oral glucose tolerance test 75 g. | Oral glucose tolerance test 75 g*. | Fasting blood glucose* | **Mother:**  Fructosamine*  HbA1c*  Leptin*, adiponectin*  **Newborn (cord):**  pH, blood glucose*  C-peptide* IGF-1*  Leptin*, adiponectin* | Capillary blood glucose | |

* : specific examinations for the study

Diabetes screening tests (oral glucose tolerance test 75 g) and fasting blood glucose tests will performed on an outpatient basis. The samples at delivery will be taken in the maternity ward (see appendix 2).

**4.6 Description of rules for temporary or permanent stopping:**

**- of a person from study participation:**

Only the withdrawal of consent can lead to a person's withdrawal from participation in the study:

**- from a part or all of the study:**

There is no justification for stopping the study.

**4.7 Data to be collected directly in the case report forms:**

- Maternal data collected at inclusion by questions about medical history and clinical examination
- Data from pregnancy follow-up:
- Monthly clinical data collection: weight, BP, proteinuria
- Results and dates of diabetes screening: fasting blood glucose, blood glucose values after oral glucose tolerance test 75 g during the second and third trimesters.
- Diabetes management: diet or insulin
- Results of ultrasound and fetal heart rate: fetal growth, malformations, vitality.
- Neonatal data:
- Apgar, cord pH
- Weight, height, head circumference
- Perinatal events: mortality, malformations, obstetric trauma, perinatal asphyxia, respiratory distress, preterm delivery, hypoglycemia
- Blood glucose values for the first 24 hours and beyond
- Hypoglycemia, blood glucose values
- Feeding during the neonatal period
- Laboratory data:
- for the mother: HbA1c, fructosamine, leptin, adiponectin
- for the newborn: cord blood glucose, C-peptide, IGF-1, leptin, adiponectin

**5. Selection and exclusion of study subjects**:

**5.1 Inclusion criteria for subjects agreeing to participate in this study:**

BMI 30 kg/m2 or between 18.5 and 24.9 kg/m2.

Pregnant women consulting at the maternity ward before 18 weeks.

Age ≥ 18 years and ≤ 40 years

Singleton pregnancy

Absence of constitutional or progressive  disease other than obesity: connective tissue diseases, chronic inflammatory diseases, epilepsy, psychiatric disease, tumor…

Provision of written informed consent.

**5.2 Criteria for exclusion of study subjects:**

BMI ≤ 18.5 kg/m2 or between 25 and 29.9 kg/m2.

Pregnant women coming for their first visit after 18 weeks

Age ≥ 18 years or ≤ 40 years

Multiple pregnancy

Constitutional or progressive disease other than obesity.

Patients who have undergone "bypass" or gastroplasty (ring) surgery for obesity.

Obesity due to genetic disease or secondary to intracranial lesions or pituitary radiation therapy.

Non-stabilized endocrine disease

Diabetes known before the pregnancy

No national health insurance coverage.

**5.3 Procedure for early withdrawal from the study or for exclusion of a study subject, and procedure for their follow-up:**

This study does not require any particular procedure in the case of a participant's withdrawal or exclusion from the research.

**6. Treatment administered to subjects agreeing to participate in this study:**

No treatment is necessary for the performance of this study.

All medication is authorized during this study, except for treatments begun before pregnancy for the treatment of a constitutional or progressive disease and for potentially teratogenic drugs.

**7. Efficacy assessment:**

**Not applicable**

8. Safety assessment:

No adverse effects specific to this study are expected. The specific maternal samples will be taken when other samples are being collected or when an infusion is being placed. The supplementary oral glucose tolerance test during the third trimester presents no special risk. The only study-specific samples for the infant will be taken from the umbilical cord after delivery and after it has been cut.

**9. Adverse effects:**

No adverse effects are expected.

**10. Statistics and data management:**

**10.1 Description of the statistical methods to be used, including the timing of any planned interim analyses.**

The study design plans to include two groups of women, obese (BMI 30 kg/m2) and non-obese (18.5 ≤BMI< 25 kg/m2).

- *Principal statistical analyses*

The principal analysis will estimate the role of maternal obesity on the newborn's body composition. We will seek specially to differentiate the attributable portion associated with obesity from that associated with diabetes. The outcome measures will be the sum of the skinfold measurements, the ponderal index, and the birth weight. We will use a covariance analysis model. Besides obesity and diabetes (no diabetes, diabetes treated by diet only, and diabetes treated by insulin), the following potential confounding factors will be introduced into the model: maternal age, hypertension during pregnancy, smoking, parity, newborn's sex, geographic origin, paternal BMI, gestational age at birth, height of father and mother, and the study center. Fetal deaths will be excluded from the analysis.

- *Secondary analyses*

- The respective roles of obesity and diabetes on the functioning of the newborn's adipose tissue, assessed by the cord blood leptin and adiponectin assays, will be estimated by analysis of variance.

- The role of growth factors such as IGF-1 and insulin (the secretion of which will be estimated by the C-peptide assay) on the newborn's body composition will be estimated by linear regression.

- The relations between the maternal metabolic indicators (leptin, adiponectin, glycosylated hemoglobin, and fructosamine) and the newborn's fat mass (quantity and functioning) on the one hand, and the newborn's growth factors (C-peptide and IGF-1), on the other hand, will also be studied by linear regression.

- The rate of hypoglycemia developing in the 48 hours after the birth of infants of obese mothers will be estimated with its 95% confidence interval.

- The rates of perinatal events in the two groups will be compared with Fisher's exact test.

- *Calendar of analyses*

No interim analysis is planned. The analysis will take place 3 years after the study begins.

**10.2 Planned number of study subjects, and planned number of subjects at each study center, with its statistical justification.**

The primary outcome measures of the study are the ponderal index and sum of skinfolds at birth. For the skinfolds, the study by Sewell et al (Am J Obstet gyneco) compared 76 overweight women (BMI ≥ 25 kg/m2) with 144 women with a BMI < 25 kg/m2. The skinfold thickness measurements at the tricipital and subscapular levels showed differences, respectively, of 0.4 mm (standard deviation of 0.95 mm) and 0.5 mm (SD 1.2), for an effect size for the two measurements of 0.42. No specific data for obese women have been presented. We have no study of the ponderal index from which we can base any hypothesis to calculate sample size. We would like to be able to show an effect size of at least 0.3 for this criterion.

To obtain a study power of 90% to demonstrate an effect size of 0.3, with an α (type 1) risk of 5%, the analysis should include a total of 470 women (235 in each of the two groups). The rate of loss to follow-up before delivery is estimated at 10%, that of fetal death at 2% (the fetal deaths will be excluded from the analyses of the anthropometric data). Because the groups are matched, we estimate the rate of women who cannot be evaluated for the principal analysis at 24%. It is therefore necessary to include 309 women in each group, for a total of 618 women.

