The neonatal particularities of infants born to obese mothers are not well known, partly because the data from the literature comes mostly from obstetric studies that provide only summary information about immediate neonatal morbidity, based on data collected in the delivery room. No available study on this subject has been conducted by a neonatology team focusing on the first days of life. At first look, the fetal and neonatal complications described in pregnancies of obese women appear analogous to those described for the children of women with diabetes during pregnancy, and the current data do not allow the determination that any specific disorder is related to maternal obesity, independently of diabetes. Nonetheless, it appears that the modifications to the intrauterine environment secondary to maternal obesity could by themselves lead to specific fetal and neonatal consequences, as shown by data about malformations. The risk of fetal malformations appears higher among obese, compared to non-obese, pregnant women; these concern primarily neural tube defects but can also affect other organs, including the heart, the gastrointestinal tract, and the lungs [7-11]. Some attribute these malformations to the frequent association between obesity and diabetes, but other studies have shown that obesity is an independent risk factor for fetal malformations [12]. Accordingly, an association with the risks of congenital diaphragmatic hernia and of omphalocele was found, neither generally reported in diabetes [8].

Some studies have shown that obese mothers' newborns have a higher birthweight and that this is related to the mother's preconception BMI (body mass index) and to her weight gain during pregnancy, independently of diabetes [13, 14]. The higher birthweight in the newborns of obese women without diabetes may be associated only with an increase in fat mass, but not lean body mass [15]. The body composition of newborns can be assessed from measurements that allow a reliable estimate of the lean and fat body mass [16]. These measurements include weight and height, from which BMI (weight/height2) and the ponderal index (weight/height3) can be calculated, as well as head circumference and the following skinfold thicknesses: tricipital, bicipital, supra-iliac, and subscapular. Estimates of the fat mass by measurement of these skinfolds and by absorptiometry correlate well [17].

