These different growth factors also play a role in glucose homeostasis. Hypoglycemia in neonates born to diabetic mothers has been widely studied and is attributed to hyperinsulinism that persists after birth. Nonetheless, a relation between the risk of hypoglycemia and the extent of macrosomia is not always observed [38]. A single study has reported a higher risk of hypoglycemia in the newborn infants of obese mothers [39]; a positive correlation has also been observed between maternal BMI at the beginning of pregnancy and umbilical cord levels of insulin and C-peptide [38].

We propose to study the newborn infants of obese women, that is, women with a preconception BMI ≥ 30 kg/m2; this criterion identifies a population of high-weight women not sufficiently accessible in general population-based studies. We start with the hypothesis that these newborns have a higher mean birthweight than those of normal-weight mothers. We want to assess the consequences of maternal obesity:

- on the newborn's weight and fat mass,
- on the functioning of the fat mass, specifically on its production of leptin and adiponectin,
- on levels of the fetal growth factors (insulin, IGF-1)
- and on the newborn's glucose metabolism.

We will determine the role of obesity and diabetes on each of these elements.

**2.2** **Summary of benefits, where appropriate, and predictable or known risks for the subjects participating in this study:**

This study comports no risk for either mother or child, and its principal objective provides no immediate benefits.

Obstetric management of the pregnancy will be according to the usual standard of care. There will be only one supplementary test, to screen for diabetes by an oral glucose tolerance test, during the third trimester; in addition, two blood samples will be taken at the same time as other samples or when starting an infusion. Their volume will be small (2 mL for the first sample, and 12 mL for the second).

The study will not modify the standard management of the newborn at all. The newborns’ blood samples for the study will come from umbilical cord blood.

The data will be used anonymously.

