**3. Study objectives:**

**The principal objective** of this project is to study whether the infants of obese mothers have differences at birth in body composition, assessed by weight and fat mass, compared with the infants of normal-weight mothers. We will focus especially on differentiating the role of maternal obesity from that of her diabetes.

**The secondary objectives** are tostudy:

- the differences in the functioning of adipose tissue of the newborn infants of obese, compared with non-obese, mothers, assessed by leptin and adiponectin assays;
- the relations between the different growth factors, such as IGF-1 and insulin, and the infant's birth weight and fat mass (because hemolysis is frequent in cord blood samples and insulin cannot be assayed in these conditions, insulin will be assessed by an assay of C-peptide, since they are present in equimolar quantities);
- the relations between the maternal metabolic indicators (leptin, adiponectin, glycosylated hemoglobin (HbA1c), fructosamine and blood glucose), the newborn's fat mass (quantity and functioning) and growth factors (C-peptide and IGF-1);
- the relations between the course of newborn's blood glucose level in the immediate postnatal period and the hormone concentrations measured in the umbilical cord blood (C-peptide, IGF-1, leptin, and adiponectin);
- estimation of the rates of perinatal mortality, morbidity, and hypoglycemia.

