**4.3 Steps taken to reduce and avoid bias:**

We will recruit control and obese women simultaneously: when a woman is included in the obese group, a non-obese woman will be included in the control group at the same maternity ward within a maximum of 7 days.

A reference midwife will note among the files of women consulting that day the women who could be included as controls because they meet the inclusion and matching criteria. When she identifies a control subject, she will inform her about the study and the protocol; the physician will collect her consent during the visit. This process will be repeated daily until a control woman is recruited.

Matching will be based initially on the obese woman's age (± 3 years), term of the pregnancy (± 2 weeks) and parity (nulliparous and primi- or multiparous).

The following confounding variables will be taken into account in the data analysis: maternal smoking, maternal diabetes, hypertension during pregnancy, geographic origin, paternal height and BMI, and the infant's sex.

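### The principal model has no maternal BMI term, so if diabetes becomes more likely with BMI inside the obese group, part of the BMI effect is likely to be credited to diabetes

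*Protocol*

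**What the plan says.** Protocol section 3 sets the emphasis of the principal objective: "We will focus especially on differentiating the role of maternal obesity from that of her diabetes". Section 10.1 repeats it for the principal analysis: "We will seek specially to differentiate the attributable portion associated with obesity from that associated with diabetes".

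The model is then specified in section 10.1. Exposure is by group: "The study design plans to include two groups of women, obese" (BMI from 30 kg/m2 upward, no ceiling) and non-obese (18.5 to below 25 kg/m2). The terms are listed: "Besides obesity and diabetes (no diabetes, diabetes treated by diet only, and diabetes treated by insulin), the following potential confounding factors will be introduced". The list goes on through maternal age, hypertension, smoking, parity and the newborn's sex, and ends with "geographic origin, paternal BMI, gestational age at birth, height of father and mother, and the study center". The father's BMI and the mother's height are in. The mother's BMI and prepregnancy weight are not.

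The confounders named in section 4.3 omit maternal BMI too: "maternal smoking, maternal diabetes, hypertension during pregnancy, geographic origin, paternal height and BMI", plus the infant's sex. Matching there is on age, term and parity. No secondary analysis in section 10.1 uses maternal BMI as a graded variable.

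On the background side, section 2.1 relates birthweight to the mother's "preconception BMI (body mass index) and to her weight gain during pregnancy, independently of diabetes", and names gestational diabetes as one of the two most frequent complications of obesity in pregnancy. Section 4.4 records measured height and prepregnancy weight at inclusion, so BMI is available for every woman.

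**The concern.** A yes/no obesity factor removes the average difference between the groups and nothing else. Within the obese group, women at 31 and at 45 kg/m2 are treated alike. If BMI within that group is related both to newborn size and to diabetes, it confounds the comparison of diabetic with non-diabetic women, and the model has no term to absorb it. The first link is stated in section 2.1 for birthweight. The second is implied by the association of obesity with gestational diabetes, although no gradient above 30 kg/m2 is given. Matching obese women to controls does not balance BMI between diabetic and non-diabetic women.

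The diabetes coefficients matter here because separating obesity from diabetes is the declared purpose, so they are not nuisance terms. The likely error is upward: diabetes would be credited with part of what belongs to higher BMI. The model also cannot show whether newborn weight or fat rises with BMI among obese women.

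**Working it through.** **The plan's own figure.** Section 10.2 gives 235 evaluable women per group for an effect size of 0.3, 90% power and two-sided 5%. Check: 2 × (1.960 + 1.282)² / 0.3² = 233.5, so 234 (normal approximation). The t-test version gives 234.5, so 235. Allowing for 24% not evaluable: 235 / 0.76 = 309.2, against 309 stated. The sample size reproduces, and this point does not affect it.

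**Form of the bias.** Let b be the outcome slope in SD per kg/m2, p the diabetes prevalence in a group, and Δ the BMI gap between diabetic and non-diabetic women in that group. With equal groups and no BMI term, the excess in the diabetes coefficient is

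bias = b × [w_ob × Δ_ob + w_no × Δ_no], where each w is proportional to p(1 − p) and the two sum to 1.

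The obesity coefficient shifts by −(p_ob − p_no) × bias.

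**Assumed inputs (none from the documents).** Diabetes in 25% of obese and 8% of control women. Obese BMI = 30 plus an exponential excess with mean 3 or 5 kg/m2; control BMI centred at 21.8. Outcome linear in BMI, with a BMI-related group difference of 0.30 or 0.42 SD (the two effect sizes in section 10.2). Diabetes odds ratio 1 to 2 per 5 kg/m2 within groups. True diabetes effect zero; diabetes entered as yes/no.

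**One case by hand.** Odds ratio 2, mean excess 5, group difference 0.42 SD:
- BMI contrast between groups: 35 − 21.8 = 13.2, so b = 0.42 / 13.2 = 0.0318.
- Weights: 0.25 × 0.75 = 0.1875 and 0.08 × 0.92 = 0.0736, so w_ob = 0.1875 / 0.2611 = 0.718.
- Simulated Δ_ob = 3.66 kg/m2, so the obese group contributes 0.0318 × 0.718 × 3.66 = 0.084 SD. The narrow control range adds little.
- The simulation gives 0.091, within its own error: 1 / √(200,000 × 0.2611) = 0.004.
- Shift in the obesity coefficient: −(0.25 − 0.08) × 0.091 = −0.015 SD.

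**Simulated diabetes coefficient without a BMI term (400,000 women per scenario, true value 0).**

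| Odds ratio per 5 kg/m2 | Difference 0.30 SD, mean excess 3 / 5 | Difference 0.42 SD, mean excess 3 / 5 |
| --- | --- | --- |
| 1 | 0.000 / −0.001 | 0.002 / 0.004 |
| 1.25 | 0.009 / 0.025 | 0.011 / 0.025 |
| 1.5 | 0.018 / 0.037 | 0.020 / 0.052 |
| 2 | 0.031 / 0.066 | 0.039 / 0.091 |

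With maternal BMI in the model the values lie between −0.005 and 0.006. A second set of assumptions (diabetes in 5-8% of controls and 15-20% of obese women, mean excess 4-6 kg/m2, true diabetes effect 0.3 SD) gives a bias of 0.013 to 0.062 SD. Over all runs with odds ratios of 1.25 to 2 the excess is about 0.01 to 0.10 SD.

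**Against sampling error.** At 235 per group with about 52 diabetic women and a true effect of 0.30, the mean coefficient is 0.342 (SE 0.151) without BMI and 0.300 (SE 0.154) with it. The obesity coefficient has SE 0.094 either way.
- Cost of the term: 0.154 / 0.151 = 1.02, about 2%.
- Root mean squared error: √(0.151² + 0.042²) = 0.157 without BMI, 0.154 with it.
- Break-even bias: √(0.154² − 0.151²) = 0.030 SD. Below that, adding BMI does not reduce the mean squared error.
- At the higher prevalences of the table the SE is nearer 1 / √(235 × 0.2611) = 0.128, so even a bias of 0.10 stays below one standard error.

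**The case against.** The strongest reply is that the result is conditional and small. Section 2.1 says that gestational diabetes is a frequent complication of obesity, not that its risk keeps rising above 30 kg/m2. With no gradient inside the group the bias is zero. Where it exists it is less than the standard error, and under weak gradients the extra term gains nothing in accuracy. All of this stands, and it sets the severity.

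A second reply is that coding of exposures is often left to the SAP, and that section 10.1 never uses the term two-level. This carries less weight. The section defines two groups, names each covariate, and includes paternal BMI and maternal height. Section 10.6 treats substantial changes to this plan as modifications to be justified in the final report. The protocol has stated a model, and that model lacks the term.

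Third, the near-zero residual bias after adding BMI partly reflects the simulation, in which the outcome is linear in BMI by assumption. Section 2.1 speaks of birthweight, and does not say that the relation is linear or that it holds for skinfolds or ponderal index. This stands too, and is why a linearity check belongs in the fix.

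A reader might infer three stronger things that the documents do not support:
- That the obesity comparison or the sample size is undermined. It is not: the obesity coefficient hardly moves.
- That the insulin-treated category is the worst affected. The calculations used diabetes as yes/no, so nothing can be said about diet versus insulin.
- That the design promised to study a gradient among obese women. Section 2.1 says of the BMI threshold that "this criterion identifies a population of high-weight women not sufficiently accessible in general population-based studies". That describes obese women as a class, not a gradient within it.

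**Conclusion.** The concern holds as a conditional one. The principal model omits maternal prepregnancy BMI while using an obese group open at the top, and its stated purpose is to separate obesity from diabetes. If diabetes odds rise with BMI within the obese group (odds ratio 1.25 to 2 per 5 kg/m2), the diabetes coefficient is likely to be too high by about 0.01 to 0.10 SD. If they do not rise, the bias is zero. The prevalences, BMI distribution, gradient and linear BMI effect behind these figures are all assumptions.

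The bias is below the standard error of the diabetes coefficient (about 0.15 SD with some 52 diabetic women), but a larger sample would not remove it. The obesity coefficient changes by at most about 0.015 SD. It would go too far to say that diabetes effects will be overstated as a matter of fact. This is a cheap improvement of minor severity, not an error that invalidates the analysis.

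**What to change.** In section 10.1, keep the obese/non-obese factor and add one term: (prepregnancy BMI − obese-group mean BMI) × obese. Centring within the obese group keeps the obesity coefficient as the average group contrast. A single linear BMI term across both groups would change its meaning, because no woman with a BMI of 25 to 29.9 is recruited. Check the within-obese relation for non-linearity, take the diabetes coefficients from this model, and report the within-obese BMI slope with its 95% confidence interval.

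The cost is a sentence in the analysis section, one degree of freedom and about 2% more standard error on the diabetes coefficient. No new data, visits or participants are needed. If the gradient proves weak there is little or no gain in accuracy, though the slope itself would still be reported.

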**2. Scientific justification and general description of the research:**

**2.1 Summary of findings from nonclinical studies and from clinical trials available and relevant to this trial:**

The proportion of women who are overweight at the beginning of their pregnancy has been increasing in recent decades. In France, the national epidemiologic survey on obesity and overweight published in September 2006 (ObEpi survey) confirmed the previously observed increase in the incidence of obesity [1]. Nearly 14 million French people are overweight or obese. This rate is increasing faster and more strongly among women than men (+64% versus +40%): 23% of women are overweight and 13% obese. These women are exposed to substantial morbidity; for those of child-bearing age, it includes complications during pregnancy.

The two most frequent complications of obesity during pregnancy are chronic hypertension with the risk of preeclampsia and gestational diabetes. Maternal obesity is also associated with a higher frequency of cesarean deliveries, fetal and neonatal deaths and malformations, and of very preterm births, as well as with a high rate of complications in the newborn, related in part to macrosomia [2-6].

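### The single principal model adjusts for diabetes and pregnancy hypertension, which section 2.1 calls complications of obesity, so on its own it does not give the overall obese-versus-normal-weight difference or the part running through diabetes

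*Protocol*

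**What the plan says.** **Aim.** Section 3 makes it the principal objective to learn whether infants of obese mothers differ at birth from infants of normal-weight mothers, with special attention to separating obesity from diabetes. Section 10.1 repeats both halves: "The principal analysis will estimate the role of maternal obesity on the newborn's body composition", and "We will seek specially to differentiate the attributable portion associated with obesity from that associated with diabetes".

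**Model.** Section 10.1 names one model: "We will use a covariance analysis model". The factors of interest come first: "Besides obesity and diabetes (no diabetes, diabetes treated by diet only, and diabetes treated by insulin". Then "the following potential confounding factors will be introduced into the model: maternal age, hypertension during pregnancy, smoking, parity", followed by further covariates that include gestational age at birth. No principal model without diabetes or hypertension is named, and no step links obesity to diabetes.

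**Labels.** Section 4.3 states: "The following confounding variables will be taken into account in the data analysis: maternal smoking, maternal diabetes, hypertension during pregnancy". Section 2.1 states: "The two most frequent complications of obesity during pregnancy are chronic hypertension with the risk of preeclampsia and gestational diabetes". Section 5.2 excludes women whose diabetes was known before the pregnancy.

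**The concern.** The exposure is prepregnancy BMI. A variable that the exposure helps to bring about is an intermediate, and adjusting for it removes from the obesity coefficient whatever part of the effect passes through it. Section 2.1 puts hypertension and gestational diabetes in that position, while section 4.3 treats them as confounders.

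Gestational age at birth is also determined after the exposure. Section 4.4 ties the target delivery date to diabetes treatment and to macrosomia, so it may absorb some of the same effect.

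What is at stake is interpretation. If obesity acts on body composition largely through diabetes, the planned obesity coefficient could be close to zero although the infants do differ. With only this model pre-stated, a null coefficient could be reported as no difference, which would be the wrong answer to the first half of the principal objective.

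**Working it through.** **1. The plan's own figure.** Inputs from sections 10.2 and 10.3: effect size 0.3, power 90%, two-sided 5%, equal groups.

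- Normal approximation: n = 2 × (1.960 + 1.282)² / 0.3² = 233.5, so 234 per group.
- With the t distribution the answer is 235 per group (power 0.901), as stated.
- Inflation for 24% not evaluable: 235 / 0.76 = 309.2, stated as 309.

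The sample size is reproduced for a two-group difference of 0.3 SD.

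**2. Order of the variables.** Exposure: BMI before pregnancy (section 2.3). Diabetes: known cases are excluded (5.2), so what enters the model was first found during pregnancy. Hypertension: recorded during pregnancy. Gestational age at birth: fixed at delivery. All three are observed after the exposure, and section 2.1 names the first two disorders as its complications.

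**3. What the coefficients contain.** Take a linear model without interaction, with one diabetes indicator for simplicity. Let *a* be the obesity coefficient, *b* the diabetes coefficient, and p₁ and p₀ the diabetes proportions in obese and control women. Then

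overall difference = *a* + *b* × (p₁ − p₀).

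The model returns *a* and *b*. The overall difference and the part through diabetes, *b* × (p₁ − p₀), also need the obesity–diabetes association or a second model without diabetes.

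**4. Two cohorts with the same coefficients.** Assumed: *a* = 0.20 SD, *b* = 0.50 SD, p₀ = 7%.

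- p₁ = 10%: 0.20 + 0.50 × 0.03 = 0.215 SD (simulation: 0.216).
- p₁ = 30%: 0.20 + 0.50 × 0.23 = 0.315 SD (simulation: 0.320).

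The fitted coefficients are about 0.20 and 0.50 in both cohorts. The planned model cannot tell them apart, although the part through diabetes is 0.015 SD in one and 0.115 SD in the other.

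**5. Power of the adjusted coefficient, illustration only.** The protocol gives no diabetes rate by group and no diabetes effect, so every input here except the 235 per group is assumed. The overall difference is set at 0.30 SD; power = Φ(d × √(235/2) − 1.96).

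| Diabetes, obese v control | Diabetes effect (SD) | Hypertension | Coefficient (SD) | Power |
|---|---|---|---|---|
| 15% v 5% | 0.3 | no effect | 0.30 − 0.03 = 0.27 | 83% |
| 30% v 8% | 0.5 | no effect | 0.30 − 0.11 = 0.19 | 54% |
| 25% v 7% | 0.5 | −0.3 SD, 15% v 5% | 0.30 − 0.09 + 0.03 = 0.24 | 74% |
| 25% v 7% | 0.25 | −0.3 SD, 15% v 5% | 0.30 − 0.045 + 0.03 = 0.285 | 87% |

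Allowing for the correlation between obesity and diabetes lowers the first two rows to 82% and 51%. Covariates that explain outcome variance act the other way. If they explained an assumed 20%, a coefficient of 0.22 SD would behave like 0.22 / √0.8 = 0.246 SD, and power would be 76% instead of 66%.

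**The case against.** The strongest reply is that adjusting for diabetes is deliberate. Section 2.1 says that existing data cannot identify effects of obesity independent of diabetes, and sections 3 and 10.1 make that separation an aim. A model holding both is the direct way to estimate the role of obesity apart from diabetes. This stands, and it is why the diabetes-adjusted model should be kept. It does not supply the overall comparison that section 3 asks for first.

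Five stronger readings are tempting but not supported:

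- *Section 10.1 treats diabetes as a confounder.* It does not: diabetes is named beside obesity, ahead of the confounder list. The label comes only from section 4.3; for hypertension it comes from both sections.
- *The model says nothing about the diabetes portion.* It returns coefficients for diet-treated and insulin-treated diabetes, and the protocol's phrase can be read as the respective roles of the two conditions. What is missing is the share of the obesity difference that passes through diabetes.
- *All diabetes in the model arises in pregnancy.* Only known diabetes is excluded, so undiagnosed earlier disease can enter. Likewise, section 2.1 speaks of chronic hypertension with a risk of preeclampsia, which is not exactly the covariate in 10.1. Possible intermediate is therefore the right label.
- *The study is underpowered.* The documents cannot show this. Section 10.2 cites 0.42 for skinfolds and sets 0.3 as a minimum target for the ponderal index, without saying whether it is adjusted. The hypertension path may run opposite to the diabetes path.
- *Gestational age at birth must be dropped.* Without it, a birth-weight difference mixes growth with timing of delivery. Either choice is defensible and answers a different question.

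The study is also observational, the variables are already collected, and section 10.6 allows justified changes. That lowers the urgency but does not replace stating the overall contrast in advance.

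**Conclusion.** The concern holds in limited form. Sections 2.1 and 4.3 give diabetes and hypertension incompatible roles. The one principal model in section 10.1 estimates at most the part of the obesity effect that does not pass through diabetes, hypertension or gestational age at birth. It answers the aim of separating obesity from diabetes. It does not by itself give the overall difference, or the part of that difference running through diabetes.

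The conclusion about what is estimated needs only the protocol's text and the decomposition above. Its size cannot be fixed from the documents: under the assumed inputs, identical model output is compatible with overall differences of 0.22 and 0.32 SD. The power figures, 54% to 87% in the table, are illustrative and do not show an error in the sample size, which reproduces. Severity: should-fix.

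**What to change.** 1. **First principal model (total effect).** Pre-state a model with obesity, the pre-exposure covariates (maternal age, parity, smoking, geographic origin, heights of both parents, paternal BMI, center) and infant sex, without diabetes or hypertension. Name it as the contrast sized in section 10.2.
2. **Second principal model.** Add the three-level diabetes factor. Report the change in the obesity coefficient with a confidence interval, and state what reading it as the part through diabetes requires: no obesity-by-diabetes interaction and no unmeasured confounding of diabetes and outcome.
3. **Further adjustments.** Show hypertension as an additional adjustment, and report results with and without gestational age at birth.
4. **Section 4.3.** Relabel diabetes and hypertension as possible intermediates, in line with section 2.1.

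The cost is one or two extra models on data already collected, some rewording, and explicit assumptions for the share through diabetes. No participant, procedure or enrolment number changes. Section 10.2 should add that its 90% power refers to the first model; power for the diabetes-adjusted coefficient cannot be stated without diabetes rates and effects.
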